## Abstract

**Objective:**

With a higher incidence rate among the younger population, cervical vertigo (CV) can impose a significant burden on patients with CV. It is believed that a deficiency of qi and blood is the primary pathogenesis in Traditional Chinese medicine (TCM). Acupuncture is a vital strategy for CV, but the efficacy of current acupuncture therapies remains unsatisfactory. Thus, this randomized controlled study will assess the safety and effectiveness of three-needle of regulating the mind combined with umbilical needle (TNRM-UN) therapy for CV with qi and blood deficiency.

**Methods:**

This was a single-center, assessor-, and analyst-blinded, prospective randomized controlled trial that involved treatment for 6 weeks and follow-up for 24 weeks. Ninety-nine patients with CV deficiency of qi and blood are randomly allocated to three groups in a 1:1:1 ratio. The patients in the observation group will receive three-needle of regulating the mind combined with umbilical needle (TNRM-UN) therapy. In contrast, the patients in the control-1 group will receive three-needle of regulating the mind combined with traditional acupuncture (TNRM-TA), and the patients in the control-2 group will receive only umbilical needle (UN) therapy. Primary outcomes include Cervical Vertigo Symptom and Functional Assessment Scale (CVS-FAS) score and qi and Blood Deficiency Symptoms Assessment Scale (QBD-SAS) score. The secondary outcomes are hemodynamic changes in the bilateral vertebral arteries, including diameter value (DV), peak systolic velocity (PSV), end-diastolic velocity (EDV), pulsatility index (PI), and resistance index (RI). All outcome measurements will be evaluated before and after 6 weeks of treatment. Primary outcomes will be evaluated at 12 and 24 weeks of follow-up. Adverse events (AEs) were evaluated during treatment and follow-up periods.

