### Outcome measures

All outcome measurements will be assessed before treatment and after 6 weeks of treatment, and primary outcomes will also be assessed at 12, 24 weeks follow-up.

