### Sample size estimation

PASS V.15.0 software (NCSS, Kaysville, UT, USA) is used for the sample size calculation, and eligible participants are separated into three groups in a 1:1:1 ratio. Owing to the lack of relevant randomized controlled trials (RCTs) and the exploratory nature of this clinical trial, we have to refer to a formula for estimating the sample size of multiple groups of randomized controlled trials: N = [(*Z*_α/2_ + *Z*_β_)σ/δ] (2) (${\text{Q}}_{1}^{-1}$ + ${\text{Q}}_{2}^{-1}$). Based on pre-experiment research data, after 20 patients received TNRM-UN treatment, the average reduction in CVS-FAS was 7.3 points, with a standard deviation of σ = 8.2; the standard deviation (σ = 8.2) in the formula is directly adopted from the pilot study to reflect population variability. Aligned with clinical consensus for vestibular disorders [Jacobson and Newman have supported using a 30%−50% reduction as clinically meaningful in vestibular outcomes in 1990 (40)], we conservatively set δ (δ = 5 points) as 60% of this observed effect. With α = 0.05, 1 – β = 0.9, and the sample number between groups Q1 = Q2 = 0.5, each group required 30 participants. Assuming a 10% dropout rate, 33 participants need to be included in each group; therefore, in total, we included 99 participants. To ensure robustness, we performed sensitivity analyses evaluating: When effect size (δ) variability was 4–6 points and standard deviation (σ) variability was 7.0 – 9.0, the results confirmed that the planned sample size (N = 99) maintained ≥80% statistical power across all plausible scenarios, supporting its adequacy even if assumptions deviated moderately from initial estimates.

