#### (2) Between-group comparisons

(a) Parametric approach: For normally distributed data with homogeneous variances, one-way analysis of variance (ANOVA) is performed. If the omnibus test is significant (*p* < 0.05), *post hoc* pairwise comparisons are conducted using Tukey's HSD to control the family-wise error rate (FWER).

(b) Non-parametric approach: For non-normal or heteroscedastic data, the Kruskal–Wallis test is applied, followed by Dunn's test with Bonferroni-adjusted *p*-values (α = 0.017).

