The innovations in the intervention approach of this study are explained as follows: Regarding the three-needle method of regulating the mind, its theoretical basis is the meridian system theory of TCM, the stimulated meridian qi is acquired meridian qi, the acupuncture site is in the brain, and the acupuncture points are located in the governor vessel. Regarding umbilical needle therapy, its theoretical basis is Yi Jing theory, the stimulated meridian qi is innate, the acupuncture site is in the umbilical region, and the acupuncture point is located in the conception vessel. Umbilical needle therapy breaks through the 1,000 of years confinement of “Shen que forbidding needles” and paves the way for the precedent of “one point curing hundreds of diseases.” This study is the first attempt to combine the two methods in treating CV. This method combines the theory of TCM and Yi Jing, the combination of the human brain and umbilical cord, the combination of the governor vessel and conception vessel, and the combination of the innate and acquired meridians. This method has the advantages of few acupuncture points, simple operation, and less pain. While it appears to be simple, it contains a great deal of theoretical basis and information, and fully embodies the holistic view of TCM and the principle of “the way is simple.”

The innovations in the control setting of this study are explained as follows: (1) The three-needle regulating the mind combined with the traditional acupuncture group was compared to the three-needle regulating the mind combined with the umbilical needle group. Both groups received initial treatment with three needles to regulate the mind for mental relaxation, and there was only a difference in the single factor of “traditional acupuncture” or “umbilical needle.” This study aimed to confirm the superiority of the umbilical needle compared with traditional acupuncture as a control. (2) The three-needle regulating the mind combined with the umbilical needle group was compared with the umbilical needle-only group. Both groups received treatment with an umbilical needle, and there was only a difference in the single factor of whether a three-needle regulating the mind was used. We propose to confirm the importance of using a three-needle to regulate the mind in CV.

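### Two unranked primary scales at three visits, with no deciding scale or visit, and family-wise control that covers only the arm pairs within a single test

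*Protocol article*

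**What the plan says.** - **Scales.** The Abstract (Methods) states: "Primary outcomes include Cervical Vertigo Symptom and Functional Assessment Scale (CVS-FAS) score and qi and Blood Deficiency Symptoms Assessment Scale (QBD-SAS) score". The section on primary outcome measures lists the same two scales without ranking them.
- **Visits.** The Outcome measures section has every measure taken at baseline and again at week 6. For the later visits it adds: "primary outcomes will also be assessed at 12, 24 weeks follow-up". Table 1 agrees, with both scales marked at weeks 0, 6, 12 and 24. None of these visits is called primary.
- **Test.** Section (2) of the Statistical analysis plan prescribes a one-way ANOVA with an omnibus threshold of 0.05. After it, in the protocol's words, "pairwise comparisons are conducted using Tukey's HSD to control the family-wise error rate (FWER"). The non-parametric route uses Dunn's test at 0.017, and the sensitivity analysis in section (4) repeats 0.017 for pairwise t-tests. No repeated-measures model is given.
- **Planning.** Sample size estimation uses CVS-FAS only: "the average reduction in CVS-FAS was 7.3 points", with an SD of 8.2 and a target difference of 5. It gives no difference or SD for QBD-SAS.
- **Aim.** Sample size estimation calls the trial exploratory. Strengths of the study says: "This study aimed to confirm the superiority of the umbilical needle compared with traditional acupuncture as a control".

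**The concern.** The article deals with family-wise error explicitly, so this is not just a detail left to a fuller document. The control it sets stops at the arm pairs inside one test. Read literally, two scales at three visits give six analyses, any of which could later be presented as the primary result. No rule says that both scales must succeed, that one comes first, or how 0.05 is shared between them.

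The trial sets out to confirm superiority, and such a claim needs an error rate that belongs to it. The nominal 5% belongs to one scale at one visit, and the protocol does not say which. The scale and visit could then be chosen after the data are seen.

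**Working it through.** **1. What the stated correction covers.** The only multiplicity figure in the document is 0.017. Three arms give three pairs, and 0.05 / 3 = 0.0167, which rounds to 0.017. Tukey's HSD spans the same three pairs. Neither reaches across scales or visits.

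**2. Number of analyses.** 2 scales × 3 post-baseline visits = 6. If only week 6 counts, 2.

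**3. Upper bound, independent tests.** P(at least one false positive) = 1 − (1 − 0.05)^k.
- k = 2: 1 − 0.95² = 9.8%
- k = 3: 1 − 0.95³ = 14.3%
- k = 6: 1 − 0.95⁶ = 26.5%

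**4. Correlated tests.** Scores on the same patients are correlated, which lowers these figures. The document gives no correlations, so those below are assumptions.

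Set-up: 3 arms × 30 (the evaluable number per group in Sample size estimation), normal data, no true effect, one-way ANOVA at 0.05, then Tukey, with 40,000 simulated trials per row. A claim favouring TNRM-UN means that the omnibus test is significant and TNRM-UN is better than at least one control by Tukey.

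| Correlation between visits / between scales | Any omnibus: one test | Any omnibus: two scales, week 6 | Any omnibus: six | Favours TNRM-UN: one test | Favours TNRM-UN: two scales, week 6 | Favours TNRM-UN: six |
|---|---|---|---|---|---|---|
| 0 / 0 | 4.9% | 9.6% | 26.4% | 1.5% | 3.2% | 9.4% |
| 0.5 / 0.3 | 5.0% | 9.5% | 23.2% | 1.7% | 3.2% | 8.2% |
| 0.6 / 0.5 | 4.9% | 9.1% | 21.4% | 1.5% | 2.9% | 7.3% |
| 0.7 / 0.5 | 5.1% | 9.2% | 19.9% | 1.7% | 3.1% | 7.0% |
| 0.8 / 0.8 | 5.1% | 7.9% | 15.4% | 1.8% | 2.7% | 5.4% |
| 0.9 / 0.7 | 5.0% | 8.5% | 14.2% | 1.6% | 2.7% | 4.7% |

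Separate simulation runs agree to within about one percentage point.

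**5. Reading.** Over six analyses, any false-positive omnibus test has a chance of about 14 to 27%, and about 20% at moderate correlation. With week 6 only it is about 8 to 10%. For a false claim favouring TNRM-UN, one test gives about 1.6%, six give about 5 to 9.5%, and two scales at week 6 give about 3%.

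**The case against.** - **Testing at each visit is inferred.** No sentence says that each scale is tested at each visit at 0.05. The later visits are described only as additional assessments. This stands. The inference rests on one-way ANOVA being the only between-group method in the section.
- **The text leans towards week 6.** It separates end of treatment from follow-up, and the pilot figure is a reduction after treatment. If week 6 decides, two analyses remain and the figures are about 8 to 10% and about 3%. This is a fair reading, but the protocol does not state it, and the deciding scale would still be open.
- **The omnibus figure counts events that the trial would not claim.** It includes TNRM-TA against UN, and results against TNRM-UN. This stands, so a reader should not infer a 20% chance of a false claim for TNRM-UN.
- **The trial is called exploratory.** That word appears where the choice of sample-size formula is explained. The stated aim of confirming superiority and the Abstract's promise of compelling evidence point the other way.
- **A fuller document may hold a hierarchy.** That is possible. But the article introduces its analysis section as detailed and sets the family-wise control there, so the gap lies in what it fixes.
- **Power.** A reader might infer that power collapses because both scales must succeed. The protocol states no such rule and gives no QBD-SAS effect, and any shortfall for CVS-FAS alone is a separate sample-size matter. No power argument is made here.

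**Conclusion.** The point holds on the text: two unranked primary scales, three visits, no deciding scale or visit, planning figures for one scale only, and family-wise control limited to the three arm pairs within one test. The primary claim therefore has no defined error rate.

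Its size depends on how the plan is read and on correlations that the document does not give. On the six-analysis reading, the error for a claim favouring TNRM-UN is roughly three to six times that of a single test (4.7 / 1.6 ≈ 3; 9.4 / 1.6 ≈ 6). On the week-6 reading it roughly doubles. The document supports neither a stated plan of six tests at 0.05 nor one exact inflation figure. Every scenario examined exceeds the single-test rate.

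**What to change.** Before any unblinded result is seen, name CVS-FAS at week 6 as the single primary endpoint, because it is the only scale with planning figures. Make QBD-SAS at week 6 the first secondary, followed by both scales at the follow-up visits in an order written down in advance. Test each step at 0.05 only if the previous one was significant, and state what counts as passing a step.

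If both scales must stay primary, apply Holm across the two at week 6 (the smaller p-value against 0.05 / 2 = 0.025, then the other against 0.05) and make the later visits secondary.

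The cost is new wording in the outcome and analysis sections and a registry update; no new data are needed. There are two real drawbacks. An isolated QBD-SAS or late-visit result can no longer be the headline. And since the stated study period is July 2023 to December 2025, the change is credible only if it is made, dated and registered before unblinding.

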**Intervention**				
TNRM-UN		O		
TNRM-TA		O		
UN		O		

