**Outcome assessments**				
(1) CVS-FAS	O	O	O	O
(2) QBD-SAS	O	O	O	O
(3) VA-DV	O	O		
(4) VA-PSV	O	O		
(5) VA-EDV	O	O		
(6) VA-PI	O	O		
(7) VA-RI	O	O		
Safety evaluation		O	O	O

O, required; TNRM-UN, three-needle of regulating the mind combined with umbilical needle; TNRM-TA, three-needle of regulating the mind combined with traditional acupuncture; UN, umbilical needle; CVS-FAS, Cervical Vertigo Symptom and Functional Assessment Scale; QBD-SAS, qi and Blood Deficiency Symptoms Assessment Scale; VA-DV, vertebral artery diameter value; VA-PSV, vertebral artery peak systolic velocity; VA-EDV, vertebral artery end diastolic velocity; VA-PI, vertebral artery pulsatility index; VA-RI, vertebral artery resistance index.

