### Intervention

Each group will be divided into 33 participants who received TNRM-UN, TNRM-TA, and UN treatments separately for 6 weeks. The frequency of the intervention is 3 times per week, and the needles are left in place for 30 min.

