### Safety evaluation

Acupuncture-associated adverse events (AEs) include intolerable pain, bleeding, local hematoma, and other uncomfortable feelings after acupuncture (e.g., pale face, cold, moist limbs, cold sweat, dizziness, nausea, rapid heartbeat, weak pulse, and even fainting). All AEs, which will be considered as unrelated, possibly related, or related to treatment, will be recorded and assessed by investigators on an adverse event. Investigators should record in detail the occurrence date, degree [mild, moderate, or severe (41)], duration of symptoms, and emergency measures of AEs.

Timely rescue measures will be taken for serious adverse events. Simultaneously, researchers will immediately report to the Ethics Committee, which will decide whether to withdraw the participants from the study.

To comprehensively assess delayed-onset AEs and acupuncture safety, we will take the following measures: (1) Extended follow-up duration: Participants will receive monthly telephone follow-ups for 6 months post-trial completion (up to week 48) to capture delayed-onset AEs. (2) Patient-reported outcome diaries: Participants will document daily symptoms (e.g., pain and numbness) in a standardized diary for 12 weeks post-treatment. (3) Electronic Health Record (EHR) Linkage: With participants' consent, we will access electronic health records for a 1-year post-trial to identify their hospitalizations or diagnoses potentially linked to acupuncture.

Standardized Criteria for AE Causality Assessment will adopt the following measures: (1) WHO-UMC Causality Criteria (42): (a) Certain: AE occurs post-treatment, aligns with known acupuncture effects, and resolves upon discontinuation. (b) Probable/likely: Temporal association with no confounding factors. (c) Possible: Plausible link, but alternative explanations exist. (d) Unlikely: No plausible connection to treatment. (2) Naranjo algorithm (43): A quantitative tool to score causality likelihood (scores: ≥5: “probable”; ≤ 1: “doubtful”). (3) Independent adjudication: A blinded Safety Review Board (SRB) comprising a neurologist, TCM expert, and pharmacovigilance specialist will resolve disputed cases.

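### The daily symptom diary starts only after the last needling session, so it covers none of the 18 sessions whose safety it is partly meant to document

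*Protocol article*

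**What the plan says.** **Treatment.** Under Intervention: "Each group will be divided into 33 participants who received TNRM-UN, TNRM-TA, and UN treatments separately for 6 weeks". And: "The frequency of the intervention is 3 times per week, and the needles are left in place for 30 min".

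**Basic AE recording.** The Safety evaluation section names the harms linked to needling: pain the patient cannot tolerate, bleeding, hematoma, and systemic reactions up to fainting. Investigators are to record all AEs, with date, severity, duration and any emergency measure. Quality control adds that AE occurrence is captured in the CRFs, and the abstract says: "Adverse events (AEs) were evaluated during treatment and follow-up periods".

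**Additional measures.** The same section then adds three measures, introduced as serving both late-onset AEs and the safety of acupuncture.
- The diary: "Participants will document daily symptoms (e.g., pain and numbness) in a standardized diary for 12 weeks post-treatment".
- Telephone calls: "Participants will receive monthly telephone follow-ups for 6 months post-trial completion (up to week 48) to capture delayed-onset AEs".
- Linkage to electronic health records for a year after the trial.

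**Schedule.** In Table 1 the row "Safety evaluation" is marked at weeks 6, 12 and 24.

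**Blinding.** Blinding method and Limitations both say that participants are not blinded. One sentence under Randomization and allocation concealment says the opposite.

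**The concern.** Most of the harms listed for acupuncture are immediate or short-lived. They occur with the needle in place, on its removal, or in the hours and days that follow. A daily diary is well suited to the mild ones felt at home, such as soreness, bruising or passing dizziness. Here it opens once needling has stopped, when few of these events can still arise.

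Three features of the plan make the choice of window matter.

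- **Safety is a stated objective**, in the abstract and again in the Conclusion.
- **Needling pain is part of the rationale.** The Introduction criticizes earlier acupuncture methods for causing more pain, and the Discussion claims less pain for the new combination. The pain items in CVS-FAS concern the neck, shoulder and head, QBD-SAS has none, and neither scale asks about pain from needling. A diary kept during treatment could inform that claim.
- **Causality assessment depends on timing.** As described, it uses temporal association and resolution once treatment stops. Dizziness and nausea are listed as AEs and are also features of the disease, so a daily record around each session would help to separate the two.

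If mild events between sessions are reported unevenly, the arms could differ in recorded AEs for reasons unrelated to true harm, because participants know what they receive.

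**Working it through.** No stated figure in the plan is at issue, so the check compares time windows.

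**Inputs**
- Sessions per week: 3 (Intervention).
- Treatment length: 6 weeks; 33 participants per arm, 99 in all (Intervention; Sample size estimation).
- Diary: 12 weeks, after treatment (Safety evaluation).
- Calls: monthly for 6 months after trial completion, up to week 48 (Safety evaluation).

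**Step 1. Exposure to needling**
- Per participant: 3 × 6 = 18 sessions.
- Per arm: 18 × 33 = 594 sessions.
- Whole trial: 18 × 99 = 1,782 sessions.

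**Step 2. Windows side by side** (diary assumed to open when treatment ends)

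| Element | Weeks from baseline | Overlap with needling |
|---|---|---|
| Needling | 0 to 6 | not applicable |
| Diary | 6 to 6 + 12 = 18 | 0 weeks |
| Monthly calls | after trial completion, to week 48 | 0 weeks |
| Record linkage | one year after the trial | 0 weeks |
| Investigator AE recording | treatment and follow-up | 6 weeks |

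All three added measures fall outside the treatment period. Only investigator recording covers it.

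**Step 3. Window against purpose**
For late-onset events, a window after treatment is coherent. For the safety of acupuncture in general, it leaves out all 18 sessions and the days between them. The diary's own examples, pain and numbness, also point to needling: the Procedures sections name numbness among the sensations that needling is meant to produce.

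**Step 4. Can the loss be sized?**
That would need an AE rate per session and the fraction of events that investigator recording misses. The documents give neither, so no number of missed events can be derived.

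**The case against.** The strongest reply is that AE capture during treatment is already provided for. The abstract covers the treatment period. The Safety evaluation section names the immediate harms and requires event-level detail for all AEs. Quality control puts them in the CRFs. The diary, calls and record linkage are additions to that base. A per-session AE prompt may also sit in the full protocol or CRF, which a condensed article need not reproduce. All of this stands, and it limits the point to the one rule that the article does fix: the diary window. It does not justify that window, because the section gives the diary a purpose beyond late-onset events.

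Three stronger readings are tempting and are not supported.

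- **A reader might infer from Table 1 that safety is assessed only once during treatment.** The table uses the same single mark in the week 6 column for each intervention, which is given 18 times. The safety mark may likewise stand for the whole period.
- **A reader might infer that events must be recalled over three to six weeks.** Participants attend three times a week, roughly every two to three days, and nothing says that AEs go unrecorded at those visits.
- **A reader might contrast zero-event 95% upper limits of 8.7% per participant (n = 33) and 0.5% per session (n = 594) to show a gain from session-level recording.** If sessions are independent, these are one limit in two units: 1 − 0.05^(1/594) = 0.00503, and 1 − (1 − 0.00503)^18 = 0.087. Neither says anything about how completely events are captured.

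**Conclusion.** The point holds in a limited form. The only daily participant-completed safety tool overlaps none of the six weeks and 18 sessions in which the listed harms mainly arise, although the plan means it to serve acupuncture safety as well as late-onset events.

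The consequence is a risk of under-ascertainment. It chiefly concerns mild, transient harms felt at home between sessions, and reporting could differ by arm because participants are not blinded. That last step follows Blinding method and Limitations over the contrary sentence on randomization. The size of the risk cannot be given from the documents.

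A reader might go further and conclude that immediate harms will be under-counted, or that the safety conclusion would rest on a period without treatment. Neither follows, because investigators are to record all AEs during treatment, with date and duration.

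The conclusion assumes that the diary opens when treatment ends, which is the plain sense of the sentence. It does not depend on any assumed AE rate or recall rate.

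**What to change.** In the Safety evaluation section, start the existing diary at the first treatment session and run it without a break to the end of the 12 weeks after treatment. State that it is used identically in all three arms and that entries are reviewed at the sessions participants already attend, so that reported symptoms reach the AE record with a date.

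The diary then runs 6 + 12 = 18 weeks in place of 12. The cost is six more diary weeks per participant and a short review at existing sessions, with no extra visit, no change to treatment and no change to the efficacy analysis.

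The stated study period began in July 2023, so some participants may already have been treated. In that case the change should take effect on one date in all arms, and diary results should be reported separately for participants treated before and after it.
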